## Abstract

**Background:**

Pancreatic resection is a major abdominal operation with 50% risk of postoperative complications. A common complication is pancreatic fistula, which may have severe clinical consequences such as postoperative bleeding, organ failure and death. The objective of this study is to investigate whether implementation of an algorithm for early detection and minimally invasive management of pancreatic fistula may improve outcomes after pancreatic resection.

**Methods:**

This is a nationwide stepped-wedge, cluster-randomized, superiority trial, designed in adherence to the Consolidated Standards of Reporting Trials (CONSORT) guidelines. During a period of 22 months, all Dutch centers performing pancreatic surgery will cross over in a randomized order from current practice to best practice according to the algorithm. This evidence-based and consensus-based algorithm will provide daily multilevel advice on the management of patients after pancreatic resection (i.e. indication for abdominal imaging, antibiotic treatment, percutaneous drainage and removal of abdominal drains). The algorithm is designed to aid early detection and minimally invasive step-up management of postoperative pancreatic fistula. Outcomes of current practice will be compared with outcomes after implementation of the algorithm. The primary outcome is a composite of major complications (i.e. post-pancreatectomy bleeding, new-onset organ failure and death) and will be measured in a sample size of at least 1600 patients undergoing pancreatic resection. Secondary endpoints include the individual components of the primary endpoint and other clinical outcomes, healthcare resource utilization and costs analysis. Follow up will be up to 90 days after pancreatic resection.

**Discussion:**

It is hypothesized that a structured nationwide implementation of a dedicated algorithm for early detection and minimally invasive step-up management of postoperative pancreatic fistula will reduce the risk of major complications and death after pancreatic resection, as compared to current practice.

**Trial registration:**

Netherlands Trial Register: NL 6671. Registered on 16 December 2017.

## Background

Without treatment, survival in patients with pancreatic cancer is only 4–6 months. Pancreatic resection combined with adjuvant chemotherapy can increase the median survival to 54 months in selected patients with pancreatic cancer [1]. Pancreatic resection is, however, a major abdominal operation that is associated with a 50% risk of complications [2]. Complications are associated with postoperative death and reduced long-term survival because patients with a complicated postoperative course are often unfit to receive adjuvant chemotherapy [3–5].

A common complication after pancreatic resection is pancreatic fistula, in which there is leakage of pancreatic juices into the abdominal cavity [6–9]. This complication is potentially life threatening due to its association with other complications. Leakage of pancreatic juices can lead to vessel erosion, potentially causing major bleeding. Systemic inflammation may result in sepsis, organ failure and death [8]. A postoperative pancreatic fistula that necessitates a change in postoperative management is regarded a “clinically relevant fistula” [10]. In a recent systematic review of 40 studies, clinically relevant pancreatic fistula occurred in 13% of patients after pancreatic resection [2]. A Dutch study (2005–2013) demonstrated that mortality in patients with severe pancreatic fistula remains as high as 18% [9]*.*

In general, in-hospital mortality after pancreatoduodenectomy varies widely among Dutch centers (interquartile range 0–8%). This variability appears to be explained by differences in failure-to-rescue rates between centers (i.e. mortality in patients with major postoperative complications) [11]. A recent multicenter propensity-score-matched study by the Dutch Pancreatic Cancer Group identified doubling of mortality after primary relaparotomy, as compared with primary minimally invasive catheter drainage for postoperative pancreatic fistula (36% vs. 14%, *P* = 0.007; risk ratio 0.39; 95% confidence interval 0.20–0.75) [9]. Relaparotomy causes a major inflammatory response syndrome in patients who are already ill, which might induce or aggravate multiple organ failure and possibly death [12]. As an alternative to relaparotomy, minimally invasive percutaneous catheter drainage has been shown to be very effective in the majority of patients [9]. In daily practice, however, both treatment strategies are still frequently performed (primary catheter drainage 73%, primary relaparotomy 27%) with no change towards a more minimally invasive management strategy [9]. This might be related to the lack of (international) guidelines on postoperative patient monitoring and management of complications.

This trial is designed to investigate whether implementation of an algorithm for postoperative care focusing on early detection and minimally invasive step-up management of postoperative pancreatic fistula results in a lower rate of major complications and death after pancreatic resection, as compared with current practice. This trial will also evaluate the superiority of the algorithm in other clinical outcomes, the number of patients receiving chemotherapy, quality of life, healthcare resource utilization and costs.

## Methods

### Trial design

This is a nationwide, stepped-wedge, cluster-randomized trial in all centers of the Dutch Pancreatic Cancer Group. The research team will implement the algorithm for early detection and minimally invasive management of pancreatic fistula to change professional behavior in each hospital and therefore stepped-wedge cluster randomization at center level will be performed. This trial was designed in accordance with the Consolidated Standards of Reporting Trials (CONSORT) guidelines for stepped-wedge, cluster-randomized trials [13] and the Standard Protocol Items: Recommendation for Interventional Trials (SPIRIT) guidelines for clinical trials (Fig. 1) [14].

**Fig. 1 Fig1:**
[figure not shown]
Standard Protocol Items: Recommendation for Interventional Trials (SPIRIT) schedule of enrollment, interventions and assessments

The stepped-wedge, cluster-randomized trial is a form of cross-over design with unidirectional cross-over (from control to intervention phase) at different time points for each cluster (Fig. 2). Each cluster will contain one center. Randomization will determine the order in which each center will undergo the transition [15, 16]. In the first timeframe, all centers will deliver current practice (i.e. control). In the second timeframe, the center in the first cluster will start with algorithm-based best practice (i.e. intervention), while all other centers will still deliver current practice. In the third timeframe, the second cluster will implement the algorithm. Following this approach, we proceed until all centers have stepped over to the algorithm. In the last timeframe, all centers will deliver treatment according to the algorithm. Each cluster will contain one center; therefore, the number of sequences is equal to the number of participating centers and this will be 17. To ensure adequate implementation of the algorithm, a wash-in period was designed in which clinicians in the center will be intensively trained by the research team on the algorithm. To avoid contamination of centers still in the current-practice phase, local clinicians will only have access to the algorithm after cross-over to care according to the algorithm.

**Fig. 2 Fig2:**
[figure not shown]
Schematic overview of trial design

### Participants

Pancreatic surgery is centralized in The Netherlands in centers performing at least 20 pancreatoduodenectomies annually. All centers performing pancreatic surgery in The Netherlands are participating in this trial. All patients undergoing all types of pancreatic resection in these centers are identified and will be recruited in this trial. There are no exclusion criteria for centers or patients (i.e. nationwide complete enumeration).

Data will be extracted from the prospective Dutch Pancreatic Cancer Audit. Additional data on clinical outcomes will be extracted prospectively through continuous systematic evaluation of patient charts using a predefined case record form. Data are stored on a central secured data capturing tool (i.e. Castor EDC) containing programmed checks for outliers. To ensure patient confidentiality, the data stored centrally will be cleaned to remove all information that could directly trace back to an individual patient, and a unique patient identifier number will be assigned to every patient. The local principal investigator will have access to the identifiable patient information. The data entered will be checked by a senior researcher. Local principal investigators are responsible for data collection. They can delegate this to the study personnel if resources are not available at the center.

### Withdrawal and replacement of centers

For the design of this trial it is essential that all participating centers participate for the entire duration of the study, to prevent an unequal distribution of patients across the two study arms (i.e. before and after implementation). If a center stops performing pancreatic surgery during the study the randomization order will be maintained. All patients treated in this center will still be included in the final analysis, according to intention-to-treat analysis. As all centers performing pancreatic surgery in the Netherlands are participating in this trial, centers will not be replaced after withdrawal.

### Intervention

This trial evaluates a nationwide cluster-level intervention in which all clinicians involved in the postoperative care of patients undergoing pancreatic resection are educated on the new algorithm for early detection and minimally invasive management of postoperative pancreatic fistula. Currently, guidelines on how to diagnose and manage postoperative pancreatic fistula are lacking. This is concerning, since management of complications appears to be the most important factor in decreasing mortality after pancreatic resection. The algorithm is based on findings in Dutch observational cohort studies, comprehensive systematic literature analyses, an inventory of current guidelines on postoperative care and expert opinion. The impact of the proposed algorithm was evaluated in a retrospective multicenter cohort and consensus upon this algorithm was reached in several plenary meetings with one pancreatic surgeon from each of the centers of the Dutch Pancreatic Cancer Group. The final algorithm was reviewed by the advisory committee of respected international experts from centers performing a high volume of pancreatic resections before implementation in this trial. As a result, we have created a best-practice algorithm based on national and international consensus. A complete overview of the design and details on the content of the algorithm are provided in Additional file 1: Appendix 1.

A schematic overview of the multilevel algorithm is provided in Fig. 3. It is based on daily standardized evaluation of all patients undergoing pancreatic resection from postoperative day 3 to discharge up to a maximum of 14 days. The algorithm will provide daily advice on three decision levels: indication for abdominal computed tomography (CT) scan (Fig. 4); indication for (invasive) intervention (i.e. minimally invasive percutaneous drainage and/or antibiotic treatment) based on evaluation of the abdominal CT scan (Fig. 5) and indication for removal of abdominal drain(s) (Fig. 6). The algorithm includes clinical data from physical examination and biochemical tests (i.e. systemic inflammatory response syndrome (SIRS), C-Reactive protein (CRP), white blood cell count (WBC), drain production including amylase content and a daily consult from a pancreatic surgeon). At predefined, evidence-based cutoff points (Fig. 4), an abdominal contrast-enhanced CT scan and possibly subsequent minimally invasive intervention should be performed or antibiotic treatment should be started (Fig. 5). Each CT scan will be evaluated according to predefined criteria (Fig. 5) to assess whether there is suspicion of a pancreatic fistula and whether there is an indication for minimally invasive percutaneous catheter drainage. In the case of no clinical improvement within 48 h after the last CT scan, a further CT scan should be performed to assess the indication for and possibility of (additional invasive) intervention. The indication to remove abdominal drains will be evaluated daily starting on postoperative day 3, for as long as there are abdominal drains in place (Fig. 6). The interpretation of the algorithm, the rationale behind the different proposed cutoff points and the proposed management of bleeding or hepaticojejunostomy leakage is provided in Additional file 1: Appendix 2. Since we propose an intervention of structured use of diagnostic and invasive interventions that are already used in daily practice, no additional harms to patients are introduced in this study.

**Fig. 3 Fig3:**
[figure not shown]
Schematic overview of algorithm. Schematic overview of the study algorithm. Daily evaluation starts on postoperative day (POD) 3 and includes vital parameters (i.e. temperature, heart rate, respiratory rate), C-reactive protein (CRP), white blood cell count (WBC), drain production, drain amylase level and a daily consult by a pancreatic surgeon. The algorithm will provide advice on three levels: indication of abdominal computed tomography (CT) scan, removal of abdominal drain(s), indication for (invasive) intervention based on systematic evaluation of abdominal CT scan

**Fig. 4 Fig4:**
[figure not shown]
Indication for computed tomography (CT) scan. Schematic overview of the indication for abdominal CT scan. °C, degrees Celsius; CRP, C-reactive protein; mg, milligram; L, liter; H, hours; WBC, white blood cell count; M, minute

**Fig. 5 Fig5:**
[figure not shown]
Evaluation of computed tomography (CT) scan. Schematic overview of the indication for (invasive) intervention based on systematic evaluation of abdominal CT scan. °C, degrees Celsius; CRP, C-reactive protein; L, liter; h, hours; WBC, white blood cell count; m, minute

**Fig. 6 Fig6:**
[figure not shown]
Removal of abdominal drains. Schematic overview of the removal of abdominal drain(s). ml, milliliter

To facilitate clinical use of this complex algorithm, it was incorporated in a smartphone application that should be filled out daily for every patient. Access to this application was granted to all clinicians participating in the trial. The application will provide multilevel advice based on the clinical and biochemical parameters entered daily. The application will not contain information that can be traced back to an individual patient. All data will be stored on a secure central database that is accessible to the study coordinators 24 h a day, 7 days a week. This was used to evaluate adherence to the study protocol. Local caregivers are contacted and reminded of the application when it is not filled out for every patient in the early afternoon, so that CT and potential drainage (if indicated) can still be performed on the same day.

Since clinical decision-making on invasive intervention in these patients is challenging, an expert panel is available to assess the indication for and feasibility of percutaneous drainage in the management of pancreatic fistula. This online panel, consisting of dedicated radiologists with expertise in abdominal radiology, interventional radiologists and surgeons with expertise in pancreatic surgery, is available 24 h a day, 7 days a week. The advice will be reported back to the clinician within 12 h after consultation or when at least three experts provide their advice on the next step in the management of these patients. The organization of this expert panel will be similar to the Dutch Pancreatitis Study Group expert panel [17].

### Outcomes

All outcomes are assessed up to 90 days after the index pancreatic resection or, if admission exceeds 90 days, up to hospital discharge. All relevant definitions are provided in Table 1. The primary endpoint is a composite of the following three major complications occurring after study intervention:
New-onset postoperative bleeding requiring invasive interventionNew-onset organ failure (i.e. pulmonary, circulatory or renal)Death

**Table 1 Tab1:** Relevant definitions

New onset	Not present any time in 24 h before study intervention; accounts for all outcomes
Mortality	Rate of death occurring within 90 days after index pancreatic resection or, if index admission exceeds 90 days, during admission
Organ failure [12]	
Pulmonary	PaO2 < 60 mmHg, despite FiO2 of 0.3, or need for mechanical ventilation
Circulatory	Systolic blood pressure < 90 mmHg, despite adequate fluid resuscitation, or need for inotropic support
Renal	Creatinine level > 177 μmol/liter after rehydration or need for hemofiltration or hemodialysis
Post-pancreatectomy hemorrhage (PPH)	Adapted from Wente et al [18]
Grade A	Occurring < 24 h after pancreatectomy (*early*) with no therapeutic consequences
Grade B	Both early (< 24 h) and late (> 24 h) requiring therapy (including fluid or blood transfusion and transfer to high-care unit), with non-life-threatening clinical condition. Includes early PPH requiring relaparotomy
Grade C	Occurring > 24 h after pancreatectomy (*late*) with severely impaired, life-threatening clinical condition requiring intervention
Comprehensive Complication Index (CCI)	This summarizes all postoperative complications, other than pre-existing complications, in a score from 0 (no complications) to 100 (death). The CCI can be readily computed on the basis of tabulated complications according to the Clavien-Dindo classification [19, 20]
Postoperative pancreatic fistula	Amylase in drain fluid on or after postoperative day 3 of at least three times the upper level of normal serum amylase [21]
Biochemical leak	Requiring no change in postoperative management, hospital stay not prolonged
Grade B	Persistent drainage > 3 weeks, change in postoperative management (i.e. catheter drainage, or angiographic procedure for bleeding, signs of infection without organ failure, no relaparotomy), all related to pancreatic fistula
Grade C	Grade B with reoperation, organ failure or death related to pancreatic fistula
Postoperative bile leakage	Bilirubin in drain fluid on or after postoperative day 3 of at least three times the upper level of normal serum bilirubin (adapted from Koch [22])
Delayed gastric emptying	Adapted from Wente et al [23]
Grade A	Nasogastric tube postoperative day 4–7 or need for replacement of tube after postoperative day 3; oral intake between day 7 and 14
Grade B	Nasogastric tube postoperative day 8–14 or need for replacement of tube after postoperative day 7; oral intake between day 14 and 21
Grade C	Nasogastric tube after postoperative day 14 or need for replacement of tube after postoperative day 14; oral intake after day 14
Gastroenterostomy leakage	As seen on abdominal imaging or during relaparotomy or secretion of fecal material from percutaneous drain or through surgical wound
Acute pancreatitis	Combination of abdominal pain, threefold increased amylase and lipase levels or as seen on radiologic imaging [24]
New-onset diabetes mellitus	Need for insulin or oral diabetes drugs within 3 months after discharge, not present before pancreatoduodenectomy
Exocrine pancreatic insufficiency	Need for oral pancreatic-enzyme supplementation within 3 months after discharge, not present before pancreatoduodenectomy
Body mass index	Weight in kilograms divided by the square of the height in meters
ASA	American Society of Anesthesiologists classification
I	Healthy patient without systemic disease
II	Patient with mild systemic disease
III	Patient with severe systemic disease, limiting activity but not life-threatening

*PaO2* arterial partial pressure of oxygen, *FiO2* fraction of inspired oxygen

The rationale for this primary endpoint is that the proposed algorithm for early detection and step-up management of pancreatic fistula can possibly prevent clinical deterioration. The most clinically severe complications associated with pancreatic fistula are combined in this endpoint [8]. Members of an adjudication committee will individually asses the primary endpoint while blinded to the assigned treatment arm; disagreements will be resolved by consensus discussions, with allocation concealment.

Secondary endpoints include individual components of the composite endpoint and an adapted version of the primary endpoint in which only complications are included that are deemed by the blinded adjudication committee to be directly related to a pancreatic fistula. Other secondary endpoints are: the Comprehensive Complication Index (CCI) [25] based on complications grade 3 or higher according to the Clavien-Dindo classification [19], postoperative pancreatic fistula [21], gastroenterostomy leakage, postoperative bile leakage [22], delayed gastric emptying [23], chyle leakage [26], new-onset acute pancreatitis [24], number and timing of abdominal CT scans, number, timing and type of invasive (re-)interventions, admission to the Intensive Care Unit (ICU), length of ICU stay, length of hospital stay, readmission rate, number of patients receiving adjuvant chemotherapy at 90 day follow up, duration of postoperative pancreatic fistula (time to removal of the last abdominal drain or completion of pancreatectomy), success of implementation (i.e. based on number and timing of abdominal CT scans and proportion of patients’ days in which the algorithm was not followed). Daily data on the incidence and duration of SIRS, sepsis and organ failure (according to the definitions in Table 1 and according to Sequential Organ Failure Assessment (SOFA) and the Multiple Organ Dysfunction Score (MODS)) are also collected [27–29]. In addition, we aim to evaluate the impact on quality of life, total direct and indirect costs and budget impact (see “Economic evaluation”).

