The primary endpoint (i.e. composite of post-pancreatectomy bleeding, new-onset organ failure and death) is a binary variable that will be analyzed using mixed-effects logistic regression analysis. Secondary endpoints will be analyzed using crude and adjusted mixed-effects logistic regression analysis (for binary outcomes) or mixed-effects linear regression analysis (for continuous outcomes). Crude analysis will include a random intercept and random slope at the level of the hospital to adjust for the design, and no other covariates. Adjusted analysis will additionally include the following covariates: calendar time and time since cross-over as a continuous variable, predictors for postoperative pancreatic fistula (i.e. soft pancreatic texture, small-diameter pancreatic duct, increasing blood loss during pancreatic resection and underlying disease that is *not* pancreatitis or pancreatic adenocarcinoma [33]) and predictors for the primary endpoint (i.e. male gender, increasing age, American Society of Anesthesiologists (ASA) classification > 2, index pancreatic resection pancreatoduodenectomy; based on multivariable logistic regression analysis as presented in Table 4). Relevant model assumptions (such as distribution of residuals) will be checked for all models; if deviations from the analysis plan are required this will be described. Crude and adjusted odds ratios with 95% confidence interval and *p* value will be reported.

**Table 4 Tab4:** Factors associated with the composite primary endpoint in 1686 patients undergoing pancreatic resection in the Dutch Pancreatic Cancer Audit

Outcome	Univariable		Multivariable	
	OR (95% CI)	*P* value	OR (95% CI)	*P* value
Male gender	1.64 (1.20–2.23)	0.002	1.64 (1.19–2.27)	0.002
Age	1.02 (1.01–1.04)	0.003	1.02 (1.00–1.03)	0.04
BMI	1.00 (1.00–1.01)	0.52		
ECOG performance score		0.17		
2 vs. 1	1.29 (0.92–1.79)	0.14		
3 vs. 1	1.59 (0.95–2.66)	0.08		
4 vs. 1	0.44 (0.06–3.33)	0.43		
ASA classification (3 and 4 vs. 1 and 2)	1.87 (1.33–2.61)	< 0.001	1.79 (1.26–2.53)	0.001
Preoperative additional nutrition		0.05		
Oral vs. none	0.98 (0.70–1.38)	0.91		
Via nasogastric tube vs. none	1.74 (0.92–3.28)	0.90		
Via TPN vs. none	4.04 (1.17–14.02)	0.03		
Preoperative biliary drainage	0.97 (0.71–1.32)	0.82		
Distal pancreatectomy vs. pancreatoduodenectomy	0.50 (0.31–0.79)	0.003	0.58 (0.36–0.94)	0.03
Texture pancreas (hard/firm vs. soft/normal)	1.22 (0.86–1.73)	0.26		

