Data from the Dutch Pancreatic Cancer Audit (2014–2015). Presented are the outcomes of univariable and multivariable logistic regression model showing gender, age, American Society of Anesthesiologists (ASA) classification and type of index resection are independently associated with the occurrence of the composite primary endpoint

*OR* odds ratio, *BMI* body mass index, *ECOG* Eastern Cooperative Oncology Group, *TPN* total parental nutrition

Length of hospital stay will be calculated from the date of the index pancreatic resection and will be analyzed using mixed-effects Cox proportional hazards regression, using discharge alive as the outcome event. Patients who die during the index hospitalization will be censored at the day of death. Length of ICU stay and time to resolution of pancreatic fistula (i.e. time to removal of the last abdominal drain or completion of pancreatectomy) will be analyzed using a zero-inflated negative binominal regression model.

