### Subgroup and sensitivity analyses

Analyses will be performed both on the group of patients undergoing pancreatoduodenectomy and on the entire group of all patients undergoing pancreatic resection. Additional subgroup analyses will be performed based on adherence to the study protocol (i.e. proportion of patients’ days in which the algorithm is followed), hospital volume (> 45 vs. ≤ 45 pancreatic resections a year), pathologic nature of disease (malignant disease), in patients with postoperative pancreatic fistula and in patients with a high risk of pancreatic fistula [34].

A sensitivity analysis will be performed to evaluate the impact on outcomes related to postoperative pancreatic fistula. To this aim, the adjudication will be asked if an outcome was related to postoperative pancreatic fistula and if this outcome could have been prevented by adherence to the algorithm. Two separate analyses will be performed on the Comprehensive Complication Index: one analysis including all complications and one adjusted analysis, in which interventions imposed by the algorithm (e.g. minimal invasive catheter drainage and use of antibiotic management for abdominal sepsis) will not be included in the calculation. A sensitivity analysis will be performed to evaluate the success of implementation. Centers will be divided into equally sized clusters based on the percentage of additional abdominal CT scans per patient after implementation, as compared with before implementation. Separate analysis will be performed for each group.

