Leakage of pancreatic enzymes causes a local inflammatory response and thereby excretion of acute-phase enzymes like C-reactive protein, release of white blood cells and clinical signs of inflammation like fever, tachycardia and tachypnea [45, 46]. Amylase levels might be elevated when measured in abdominal drain fluid [10]. The abdominal drain might, however, not be in an adequate position to drain pancreatic leakage. In addition, abdominal drains are becoming more frequently omitted at the time of pancreatic resection or are removed in the early postoperative phase [47]. In these patients, signs of inflammation are the only early signs of postoperative pancreatic fistula. These signs are, however, nonspecific and often not recognized as potential pancreatic leakage, especially in centers where only a few patients with pancreatic fistula are seen annually [45]. We believe, however, that in these patients with a high risk of life-threatening complications, early abdominal CT should be performed and peripancreatic fluid collections should be managed aggressively with percutaneous drainage in patients showing signs of systemic inflammation [9, 48, 49]. This might result in an increased use of abdominal imaging and percutaneous catheter drainage procedures in the entire study population, with the intention of reducing severe bleeding, organ failure or mortality in a subset of patients. The outcomes of this trail will provide more insight into the “number needed to scan” or “number needed to drain” and the cost-effectiveness of intensified postoperative monitoring.

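### By the plan's default rule, timing of CT and of re-interventions is compared only among patients who had one, a group the algorithm is expected to change

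*Protocol article*

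**What the plan says.** The Outcomes section of the protocol article lists among the secondary endpoints "number and timing of abdominal CT scans, number, timing and type of invasive (re-)interventions". The same section uses CT timing a second time, for "success of implementation (i.e. based on number and timing of abdominal CT scans" and the share of patient-days on which the algorithm was not followed.

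The Statistical analysis section gives one general rule for secondary endpoints: mixed-effects logistic regression for binary outcomes and "mixed-effects linear regression analysis (for continuous outcomes"). It then names three exceptions. Length of hospital stay "will be analyzed using mixed-effects Cox proportional hazards regression, using discharge alive as the outcome event". "Length of ICU stay and time to resolution of pancreatic fistula" go to a zero-inflated negative binomial model. Timing of CT and of interventions is not among the exceptions.

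On the effect of the algorithm on scanning and drainage, the Discussion says: "This might result in an increased use of abdominal imaging and percutaneous catheter drainage procedures in the entire study population". The implementation analysis in Subgroup and sensitivity analyses groups centers by the "percentage of additional abdominal CT scans per patient after implementation", relative to before. The Intervention section describes "daily standardized evaluation of all patients undergoing pancreatic resection from postoperative day 3 to discharge up to a maximum of 14 days".

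**The concern.** A patient who is never scanned has no day of scanning, and a patient who is never drained has no day of drainage. A linear model of timing therefore runs on those who had the event. Having the event comes after allocation, and the algorithm is meant to act on it through its daily indication for CT. The scanned patients after cross-over are then a different selection from those before. The added patients can pull the mean day down or up even if everyone who would have been scanned anyway is scanned on the same day as before.

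Early detection is the mechanism by which the algorithm is supposed to work, and CT timing is one of the measures of whether it was implemented. A difference in mean day among scanned patients could be read as earlier or later detection when it reflects only who was scanned.

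**Working it through.** **Step 1: which model applies.** Timing is a continuous quantity. The general rule assigns continuous secondary endpoints to mixed-effects linear regression, and the three named exceptions leave timing out. The linear model follows by default; no sentence assigns it to timing directly.

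**Step 2: the shift from selection alone.** The documents contain no scan rate and no scan day, so there is no figure of the plan to reproduce here and every input below is an assumption. The plan does not say which scan counts; I take the first.

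- b = proportion scanned under current practice
- s = further proportion scanned only under the algorithm
- U = mean day of usual scans, the same in both phases
- A = mean day of added scans

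Mean before = U. Mean after = (b·U + s·A)/(b + s). Shift = s/(b + s) × (A − U).

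With b = 0.40, s = 0.20 and U = 7:

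- A = 4: (0.40 × 7 + 0.20 × 4)/0.60 = 3.6/0.60 = 6.0, a shift of −1.0 day
- A = 10: (0.40 × 7 + 0.20 × 10)/0.60 = 4.8/0.60 = 8.0, a shift of +1.0 day
- A = 7: no shift

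**Step 3: range.** With U = 8, the shift in days is:

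| b | s | A = 4 | A = 6 | A = 12 |
|---|---|---|---|---|
| 0.30 | 0.10 | −1.00 | −0.50 | +1.00 |
| 0.30 | 0.30 | −2.00 | −1.00 | +2.00 |
| 0.40 | 0.20 | −1.33 | −0.67 | +1.33 |
| 0.50 | 0.10 | −0.67 | −0.33 | +0.67 |

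Over b = 30–50%, s = 10–30% and A = 4–6, the shift runs from −0.33 to −2.0 days.

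**Step 4: does the stepped-wedge adjustment remove it?** A simulated trial had 17 centers, 18 periods and 4 patients per cell, with 300 runs per scenario. Usual scans fell on day 3 plus an exponential time with mean 5 (so U = 8), and added scans on day 3 plus an exponential time with mean A − 3. The between-center standard deviation was 0.5 day. No existing scan was moved. Scan day in scanned patients was regressed on phase, linear calendar time and center fixed effects.

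| b, s, A | Mean estimate (days) | Runs with p < 0.05 |
|---|---|---|
| 0.40, 0.20, 4 | −1.32 | 50% |
| 0.40, 0.20, 5 | −1.03 | 36% |
| 0.40, 0.20, 8 | 0.00 | 7% |
| 0.40, 0.20, 12 | +1.28 | 29% |
| 0.30, 0.30, 5 | −1.49 | 60% |

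Among patients who would have been scanned anyway, the estimates lay between −0.09 and +0.01 day, significant in 4–8% of runs. Adjustment for center and time leaves the selection effect in place. The simulation used center fixed effects, not the planned random intercept and slope. The rejection rates also depend on the assumed spread of scan days.

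**Step 5: what an all-patient analysis measures.** If 40% are scanned before and 60% after, the proportions never scanned are 0.60 and 0.40. Under proportional subdistribution hazards the ratio is ln(0.40)/ln(0.60) = 0.916/0.511 ≈ 1.8, whichever patients account for the increase. The measure is defined for everyone, but it combines more scanning with earlier scanning.

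**The case against.** **The model is inferred.** The article never says that day of first CT will be averaged among scanned patients. Its general rule reads as a summary, since numbers of scans and types of intervention fit neither of its two classes well. The full protocol and any separate analysis plan may define timing differently. This stands as a limit: a reader might infer that the article expressly chooses this analysis, and it does not. But the rule as published, with its named exceptions, leads there. The allowance for deviations is tied to checks of model assumptions, such as residuals, which would not reveal this selection.

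**Number is reported next to timing.** A change in scan day would appear beside the change in scan count, and the implementation analysis that groups centers uses additional scans, not timing. This helps a careful reader, but it does not make the timing estimate comparable between phases.

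**An all-patient analysis does not separate the two effects either.** This stands, as step 5 shows. Its advantage is that all patients enter both phases, so the comparison is not conditioned on an event the algorithm changes.

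**Discharge is not an end of risk.** Outcomes are followed to 90 days and readmission is itself an endpoint, so scans and drainages after discharge count. Treating discharge as a competing event would drop them and tie the result to length of stay. This stands and shapes the fix.

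**The size is assumed.** This stands too. The same formula gives a negative shift, a positive shift or none, depending on when the added scans fall.

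**Conclusion.** The concern holds in a limited form. Under the default rule, timing of CT and of invasive interventions is compared between differently selected patients, because the algorithm is expected to increase both. The mean day can shift without any existing scan moving. With 40% scanned before and 20% added, a 3-day gap between added and usual scans gives 1 day; the actual size and sign are unknown.

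A reader might infer that the algorithm will falsely appear to bring scans forward. The documents do not support that. It would require added scans to fall earlier than usual ones. Evaluation from day 3 makes that plausible, but no data in the article show it, and later added scans would produce an apparent delay. A reader might also infer that the main result is at risk. It is not: this concerns secondary endpoints only, and the composite primary endpoint and the sample size of 1186 do not depend on it.

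**What to change.** Add timing of CT and of invasive (re-)interventions to the named exceptions in Statistical analysis:

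- Analyse time from resection to first abdominal CT, and to first invasive (re-)intervention, in all patients over the 90-day follow-up. Death is the competing event, and discharge does not end follow-up. Use the same hospital and calendar-time terms as the adjusted secondary analyses.
- Report the cumulative proportion scanned and the cumulative proportion drained by fixed postoperative days, and use these for the timing part of success of implementation.
- Present timing among patients who had the event as descriptive only, next to the proportion who had it.
- State that the all-patient measure combines more scanning with earlier scanning and does not show that the same patients were scanned earlier.

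The cost is a change of wording and one additional model. Timing is already a planned endpoint, so the dates should be available. The downside is a combined rather than a separate measure of timing.
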